Therefore, the primary objectives of this protocol are to (i) validate gait characteristics from CuePD and (ii) evaluate the effects of personalised auditory cues (metronome beats, instrumental music, and vocal music) to retrain and improve gait in a lab, i.e., increase gait speed, cadence and stride length while reducing gait variability. Our secondary objectives are to assess recruited PwPD and their (a) acceptance and preference of personalised music cues compared to traditional metronome cueing while (b) understanding their ability to adhere to cues due to their musicality.

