#### Walking/gait tasks.

Participants will choose from a selection of music tracks that span genres including pop, rock, R&B, and country. All walks will be 1-minute in duration in a continuous 25m loop, including two 8.5m straight segments and two 4m turns, Fig 3. Walk #1 will be at the participant’s natural walking pace to calculate a baseline cadence, i.e., a walk with no cueing (NC). Walks #2, #4, and #6 will be cued, with external auditory stimuli (BPM set at +10% of baseline cadence) which are metronome (Me), instrumental music (IM), and vocal music (VM). Participants will be assigned to one of three counterbalanced cue sequences for Walks #2, #4, and #6. For example, the first participant enrolled to the study follows Sequence 1, the second follows Sequence 2, the third follows Sequence 3, and the fourth cycles back to Sequence 1, etc.

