#### Impact of cueing.

This examines the ability of different personalised auditory cues to modify/retrain gait in PwPD. By comparing the effects of metronome beats, instrumental music, and vocal music on gait speed, stride-time variability, and stride length, this outcome seeks to identify which auditory cues most effectively enhance gait stability and performance. ${\text{Coefficient of variance of stride}-\text{time }(\text{CV}}_{\text{stride}-\text{time}})$ will be calculated as the standardised measure of the dispersion of stride times. This provides a more reliable measure of stride-time variability and has shown to be a significant indicator of gait instability and an independent predictor of fall risk among older adults and PwPD, underscoring its importance in clinical and rehabilitative settings [73]. Measuring changes in gait will be key to assessing CuePD as a gait retraining tool.

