#### Adherence to cues and musicality.

Adherence will be treated both as a continuous variable (percentage change in cadence from baseline) and as a binary variable for group comparisons. The primary binary adherence definition is: adherent = ≥5% increase in cadence from baseline; non-adherent = < 5%. Mann–Whitney U tests will compare Gold-MSI between adherent and non-adherent participants. Participants with missing baseline or intervention-based cadence (e.g., wishing to withdraw or technology failure) will be excluded from binary adherence analyses and numbers excluded will be reported.

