#### Sample size.

Sample size calculations were based on detecting changes in gait speed using a within-subject design. Assuming a standardised response mean (SRM) of 0.5 (moderate effect size) for gait speed, a two-sided significance level (α) of 0.01, and 90% power, approximately 54 participants would be required to detect a statistically significant change in gait speed for a single comparison (e.g., cued vs. non-cued walking). When accounting for the three cueing conditions and the associated adjustment for multiple (three) comparisons, we applied a Bonferroni correction resulting in an adjusted alpha of α (0.01/3 = 0.0033). That requirement increases sample size to approx. 55 participants. However, to allow for an anticipated attrition rate of up to 10%, we plan to recruit 60 participants in total. This sample size ensures adequate power to detect moderate cueing effects on gait speed, accommodates potential dropouts, and provides balanced representation across randomisation sequences.

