### Statistical analysis

For the first primary objective, all gait characteristics derived from CuePD and reference will be compared using ICC_2,1_ (absolute agreement), a two-way random-effects model for single measures that evaluate the absolute agreement between raters. The level of agreement will be interpreted as: < 0.5 shows poor agreement, 0.5–0.75 moderate, 0.75–0.9 good and 0.9–1.0 excellent. PCC’s will be calculated to measure the linear correlation between the two sets of results. Correlation coefficients will be interpreted as follows: zero (0), weak (±0.1 to ±0.3), moderate (±0.4 to ±0.6), strong (±0.7 to ±0.9), and excellent/perfect (+1 or −1).

The median, mean, standard deviation (SD), minimum/min, maximum/max, and standardised response mean (SRM) of cadence, stride length, gait speed and CV_stride-time_ will be calculated. These descriptive statistics will provide context for interpreting changes and help to clarify the magnitude and consistency of cueing effects. SRM allows for assessment of responsiveness and comparison of results to other studies. The SRM will be interpreted as: > 0.8 large positive response, 0.5–0.8 moderate responsiveness, and <0.5 low responsiveness where positive values imply an improvement for cadence, gait speed and stride length but negative is an improvement for CV_stride-time_, i.e., reduces variability.

To evaluate the cueing modality adherence, the percentage change in cadence from the baseline walk to each cueing modality will be calculated for each participant. The most effective cueing modality will be identified as the one producing a change closest to 10%.

Model assumptions will be formally checked, where residual normality and normality of gait characteristics within each cue condition will be assessed using the Shapiro-Wilk test, and sphericity with Mauchly’s test. The Greenhouse-Geisser correction will be applied if sphericity is violated.

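### Cadence is the instructed task, yet the plan counts it as gait improvement and names the most effective cue on cadence alone, against its own outcome section

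*Protocol article*

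**What the plan says.** Walking/gait tasks sets all three cues to the same tempo ("BPM set at +10% of baseline cadence"), and the instruction on each cued walk is to keep to the beat. The resulting cadence change is used in three roles.

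- **Adherence.** Statistical analysis introduces it this way: "To evaluate the cueing modality adherence, the percentage change in cadence from the baseline walk to each cueing modality will be calculated". Adherence to cues and musicality adds a binary version: "adherent = ≥5% increase in cadence from baseline". The musicality analysis uses the absolute deviation from the +10% target.
- **Improvement.** The Introduction lists cadence among the gains to be shown, first in describing the study's focus and then in primary objective (ii): "retrain and improve gait in a lab, i.e., increase gait speed, cadence and stride length while reducing gait variability". Statistical analysis gives the scoring direction for the standardised response mean (SRM): "positive values imply an improvement for cadence, gait speed and stride length".
- **Effectiveness.** Statistical analysis: "The most effective cueing modality will be identified as the one producing a change closest to 10" (per cent). Nothing else enters this rule.

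Elsewhere cadence is left out. In Impact of cueing, the cues are compared on gait speed, stride-time variability and stride length, and "this outcome seeks to identify which auditory cues most effectively enhance gait stability and performance". The Abstract defines better gait by speed, stride length and variability. The musicality analysis lists speed, stride length and the coefficient of variation (CV) of stride time as its gait improvements.

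**The concern.** A quantity that participants are instructed to change cannot also be independent evidence that the change did them good. Two consequences follow.

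First, the plan has two bases for calling a cue most effective: closeness to a tempo target, and change in three gait outcomes. They need not agree, and nothing says which one governs. The cadence rule also sits badly with the SRM direction in the same section. There a larger cadence rise is better, whereas under the closest-to-10% rule a cue that produces +14% loses to one that produces +10%.

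Second, gait speed is the sizing outcome ("Sample size calculations were based on detecting changes in gait speed using a within-subject design") and contains cadence as a factor. The comparison of cued with uncued walking can therefore be positive through tempo alone, with no gain in stride length.

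At stake is what the trial can say about its cues. A reader told that one cue was most effective will take it to mean better gait, when the rule establishes only that the tempo was matched.

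**Working it through.** The plan gives no figure for this point; it rests on a decision rule. The sample-size numbers are not needed here, and the planning SRM of 0.5 (Sample size) serves only as a yardstick.

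**1. How speed depends on tempo.** Speed = cadence × stride length / 2. With proportional changes c in cadence and s in stride length, the change in speed is (1 + c)(1 + s) − 1.

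- c = +10%, s = 0: speed +10%.
- c = +10%, s = −5%: 1.10 × 0.95 = 1.045, speed +4.5%.
- c = +10%, s = −8%: 1.10 × 0.92 = 1.012, speed +1.2%.
- Break-even s = 1/(1 + c) − 1. At c = +10% this is 1/1.10 − 1 = −9.1%. At c = +5%, the plan's threshold for adherent, it is 1/1.05 − 1 = −4.8%.

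**2. Can the two rules name different cues?** The cadence, stride-length and CV changes below are assumed for illustration; the documents give none. Speed follows from step 1.

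| Cue | Cadence | Stride length | CV stride-time | Speed | Distance from 10% |
|---|---|---|---|---|---|
| A | +10% | −5% | +20% | 1.10 × 0.95: +4.5% | 0 |
| B | +6% | +3% | −10% | 1.06 × 1.03: +9.2% | 4 points |
| C | +14% | +2% | −5% | 1.14 × 1.02: +16.3% | 4 points |

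The cadence rule names A. On the three outcomes in Impact of cueing, A is the worst of the three on every one. So the rules can disagree, and the cadence rule can pick a cue under which strides shorten and variability rises.

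**3. How much SRM could tempo alone supply?** SRM = mean % change in speed / SD of % change in speed. Stride length is held unchanged. The SDs and the mean cadence gains are assumptions.

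| SD of % speed change | 10 | 15 | 20 | 25 |
|---|---|---|---|---|
| Mean cadence gain 10% | 1.0 | 0.67 | 0.50 | 0.40 |
| Mean cadence gain 5% | 0.50 | 0.33 | 0.25 | 0.20 |

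Tempo alone reaches the planning SRM of 0.5 if the SD is at most 20 points under full compliance (10/20), but only if it is at most 10 points under half compliance (5/10).

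**The case against.** The strongest reply is that the disputed sentence comes straight after one about adherence, so the natural reading of most effective is best followed. That may well be the intent. But the sentence does not say so, and it uses the same notion of effectiveness as the aim in Impact of cueing. If best followed is meant, relabelling costs nothing.

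A reader might go further and infer that primary objective (ii) can be declared met merely because participants obeyed the tempo. The documents do not support that. The definition in the Introduction is conjunctive: speed, cadence and stride length up, and variability down. Quicker, shorter, more irregular steps fail two of its four parts, and no section declares the objective met on cadence or speed alone. Stride length and CV of stride time are analysed and reported as separate outcomes, so a worsening would be visible. The Discussion also warns against reading the results as proof that one cue is superior. All of this stands and limits the harm, but none of it lets a worsening change the label.

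Nor do the documents predict shorter strides. The Smartphone and CuePD section cites +10% as promoting longer strides, higher speed and lower variability. A speed gain reached partly through cadence is a real gain, not a measurement artefact, and gait speed is a legitimate outcome. Since all cues share one tempo, the built-in effect bears mainly on cued against uncued walking. However, the primary comparisons appear to be of that kind: Sample size gives cued versus non-cued as its example, and comparisons between cues are listed as secondary.

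**Conclusion.** The point holds, at moderate severity. As written, Statistical analysis names the most effective cue by cadence alone, although cadence is the assigned task, and this conflicts with Impact of cueing. Counting higher cadence as improvement in the Introduction and Statistical analysis also conflicts with the Abstract, Impact of cueing and the musicality analysis.

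The break-even figures (9.1% stride shortening at +10% cadence, 4.8% at +5%) follow from the speed identity and need no other assumption. They show that a positive cued-versus-uncued speed result does not by itself demonstrate longer strides. The SRM attributable to tempo is conditional: 1.0 to 0.40 with a mean cadence gain of 10%, or 0.50 to 0.20 with a gain of 5%, for assumed SDs of 10 to 25 points and unchanged stride length. The three-cue table shows what can happen, not what is expected. No planned test is shown to be invalid; what is at fault is the label and the meaning attached to cadence and speed.

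**What to change.** 1. In Statistical analysis, rename the closest-to-10% rule as identifying the best-followed (highest-adherence) cueing modality. Base any statement about the most effective cue on the outcomes already named in Impact of cueing: gait speed, stride length and CV of stride time.
2. In the Introduction (study focus and primary objective ii) and in the SRM interpretation, treat cadence change as the adherence or manipulation check and remove it from the definition of improvement. This brings them into line with the Abstract, Impact of cueing and the musicality analysis.
3. Report each gait-speed change beside its two parts: change in log speed = change in log cadence + change in log stride length. Gait speed stays as an outcome.

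The cost is rewording and one derived table from data already collected. The downside is that some speed gains will be shown to be tempo compliance, so the headline may look less favourable. Neither the cue tempo nor the walking procedure is in question.

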## Materials and methods

### Study design

This is a crossover interventional design study conducted in a controlled gait laboratory setting. It aims to assess and validate participants’ responses to different auditory cues, such as metronome beats, instrumental music, and vocal music, while walking under controlled conditions. The lab environment allows for precise measurements of gait characteristics, providing detailed insights into the use of personalised auditory cues in regulating the gait of PwPD. As this is a study protocol, no data have been included, and it conforms to PLOS data policy.

### Ethical approval

An ethics application (Ref: 3231) was submitted to Northumbria University research internal ethics committee and approved (06-03-2023). The study received NHS research ethics committee approval (REC, Ref: 24/PR/0684) via the Integrated Research Application System (IRAS, Ref: 327241) and a Health Research Authority (HRA) letter of approval, 25 July 2024. The authors confirm that all ongoing and related trials for this intervention are/will be registered. This trial was listed on the ClinicalTrials.gov registry with study ID NCT06941779 on 24 April 2025. The trial team was unaware of the requirement to register prior to participant recruitment and completed registration as soon as this oversight was recognised.

### Participants

Sixty (60) PwPD will be recruited for this study, with no specific criteria for recruitment regarding gender or sex.

### Recruitment

Participants will be recruited through the Dementias & Neurodegenerative Diseases Research Network (DeNDRoN) Research Case Register, which includes PwPD with confirmed diagnoses interested in local research. Additionally, participants may be identified through the movement disorders clinics within Northumbria Healthcare NHS Foundation Trust. Interested participants will be provided with a REC approved Participant Information Sheet. Recruitment opened in September 2024 and will terminate in December 2025 where results are expected in February 2026. Before participating in the study, written, informed consent will be obtained from all participants. Table 1 outlines the inclusion and exclusion criteria for the study. No hearing inclusion criterion (e.g., whisper test) is included because the intervention (CuePD) delivers adjustable-volume rhythmic cues via headphones/speakers, enabling participants with mild hearing impairment to perceive and respond to the beat. Excluding such individuals would unnecessarily limit recruitment and reduce generalisability, while the ability to perceive speech at 2 m is not directly relevant to rhythm entrainment for gait training.

**Table 1 pone.0346508.t001:** Study inclusion and exclusion criteria.

Inclusion criteria	Exclusion criteria
• Aged ≥50 years • Able to walk unaided. • Diagnosis of idiopathic PD, as defined by the UK Brain Bank criteria. • Score ≥21/30 on Montreal Cognitive Assessment (MoCA) which is used to classify non-demented PD (PD dementia is < 21/30).	• Non-English speakers • History of stroke, traumatic brain injury or other neurological disorders (other than PD) • Acute lower back or lower extremity pain, peripheral neuropathy, and musculoskeletal disorders that would affect tasks. • Unstable medical condition including cardio-vascular instability in the past 6 months • Unable to comply with the testing protocol or currently participating in another interfering research project

### Equipment

The equipment used in this study includes a (i) smartphone with the CuePD app installed, (ii) reference IMU wearable, (iii) a pair of wireless headphones and (iv) a belt attachment with phone holder. The placement and orientation of these devices are illustrated in Fig 1.

**Fig 1 pone.0346508.g001:**
[figure not shown]
Equipment Configuration for the Study. This figure displays the setup of the smartphone device with CuePD installed, reference IMU wearables, a pair of wireless headphones, a belt, and a phone holder as used in the experiments.

#### Reference standard.

The reference for this study is Opal (https://clario.com/solutions/precision-motion-for-research/) which interfaces with Mobility Lab, a validated commercially available system that enables comprehensive gait assessment [22]. It allows for the wireless synchronisation of up to six IMUs (Opal V1), which incorporate tri-axial accelerometers (range:  ±  16g and  ±  200g), gyroscopes (range:  ±  2000°/s), and magnetometers (range:  ±  8 Gauss). During each walking task, a single Opal IMU (26g, 50 × 40 × 14 mm), sampling data at 128 Hertz/Hz, will be attached to the talus joint of each foot of the participant. Reference standard data will be used to validate CuePD’s temporal, spatial, and spatiotemporal gait characteristics (inc. asymmetry and variation) in PwPD to ensure primary outcomes are robust.

#### Smartphone and CuePD.

CuePD will be installed on an Apple iPhone XS (177g, 143.6 × 70.9 × 7.7 mm), which has embedded tri-axial accelerometer and gyroscope inertial sensors, sampling data at ±8 g and 100 Hz. The smartphone will be securely attached to the participants’ lower back at the 5th lumbar vertebra (L5) using a belt strap and phone holder. The app, built in React Native with JavaScript, uses the API ‘react-native-sensors’ to capture tri-axial accelerometer data at a frequency of 100 Hz, providing high-resolution motion data. It includes a countdown for data recording, initiated by a user prompt, and after each one-minute session, it transmits the data to a Python server on Azure through a RESTful API using HTTP POST requests. This server, deployed on an Azure virtual machine running Ubuntu 20.04, utilises Flask to handle incoming requests and process the gait characteristics using NumPy [48], SciPy [49], and PyWavelets [50] libraries for signal processing. The processed data is stored in a PostgreSQL database hosted on Azure, ensuring reliable data management and retrieval. The server then sends the calculated gait characteristics back to the phone through the same RESTful API.

All audio files for each cueing mechanism are stored as. MP3 files and hosted on Azure Blob Storage, ensuring scalability and durability. When the user initiates cueing on the app, the server retrieves the audio files and estimates the beat per minute (BPM) of the audio file using Librosa, an audio signal analysis library in Python [51]. The server then adjusts the tempo of the audio using the FFmpeg Python library, which provides a reliable time-stretching algorithm [52]. This adjustment aligns the music's beats-per-minute with the user's steps-per-minute (SPM) plus an additional 10%, which has been found effective in promoting longer strides, increasing gait speed, and reducing variability [53–59]. The processed audio file is then re-encoded as. MP3, saved back to the Azure Blob Storage and then sent to CuePD for playback. All participants will wear headphones, cleaned between participants, and comfortably placed on their head over their ears to listen to cueing modalities. For more details on CuePD, read here [60–62].

### Data collection

All testing will be conducted at the Clinical Gait Laboratory, Coach Lane Campus, Northumbria University, Newcastle upon Tyne. Fig 2 outlines the SPIRIT schedule of enrolment, interventions and assessments. Upon attending the gait lab informed written consent procedures will be undertaken, and then participants will be required to answer questionnaires as follows (with i to vii pre and viii to ix post-gait tasks):

**Fig 2 pone.0346508.g002:**
[figure not shown]
SPIRIT schedule of enrolment, interventions, and assessments. *Order of cued walks are allocated at enrolment.

(i)**Montreal Cognitive Assessment (MoCA)**: Administered as a screening tool to exclude those with cognitive impairment with <21 being a cut-off point for PwPD. The MoCA will be used as a standardised neuropsychological test acknowledged as a valid and efficient tool for the rapid screening of global cognitive dysfunction [63]. It is used to examine diverse cognitive domains including attention and concentration, executive functions, memory, language, visuo-constructional skills, conceptual thinking, calculations, and orientation.(ii)**Participant Demographics:** (a) Height and weight, (b) age, (c) ethnicity, (d) duration of PD diagnosis.(iii)**Education level**: (a) pre/post-high school, (b) college or (c) university(iv)**Physical activity levels**: To concisely capture physical activity across a range of habitual tasks, two questionnaires will be used: (i) a physical activity questionnaire for the elderly with a reference period of 1-year was used to understand functional household (e.g., cleaning) and community-based activities (e.g., shopping [64]), and (ii) the International Physical Activity Questionnaire Short Form (IPAQ-SF), to assess the types of intensity of physical activity and sitting time to estimate total physical activity in MET-min/week and time spent sitting [65].(v)**Falls history**: Falls incidence, cause, location and consequences in the previous 12-months will be assessed by a questionnaire based on recommendations [66,67], that leads with the question “In the past year, have you had any fall including a slip or trip in which you lost your balance and landed on the floor or ground or lower level?” [68].(vi)**Falls Efficacy Scale – International Version (FES-I)**: Used to measure fear of falling in the PwPD [68]. This short, validated measure will assess fear of falling during both basic and demanding activities (physical and social) using a scale from 1 (Not at all concerned) to 4 (Very concerned) across 16 scenarios.(vii)**MDS-Unified Parkinson's Disease Rating Scale (MDS-UPDRS)**: Commonly employed to evaluate both motor and non-motor symptoms associated with PD [69]. This scale consists of four main sections, each targeting a specific area of evaluation. The first part examines non-motor experiences that occur during daily living, while the second part assesses motor experiences during daily living. The third part evaluates motor examination, while the fourth part focuses on assessing complications related to therapy. To determine the severity of the symptoms, the UPDRS is scored based on a total of 195 points, where higher scores suggest increasing levels of disability.

After completion of all walks, participants will complete:

(viii)**Goldsmiths Musical Sophistication Index (Gold-MSI)**: A 39-item (scored from 1 to 7) self-report designed to assess musicality across five subscales: active engagement (AE), perceptual abilities (PA), musical training (MT), singing abilities (SA), and emotional response (ER) to music [70]. This tool evaluates and provides the detailed extent and nature of musical experiences and skills, but also provides a broader score on musicality, General Music Sophistication (GMS), ranging from 32 to 126. For this study, the scale will be used to assess if there was a relationship between an individual’s general music sophistication and their adherence to the beat of the music cues. Furthermore, the relationship between an individual’s subscale results and beat adherence will also be assessed.(ix)**System Usability Scale (SUS):** This will evaluate perceptions of the app’s usability, complexity, and overall satisfaction [71]. The SUS produces a composite score that ranges from 0 to 100, calculated by first adjusting the responses from a set of ten questions. For odd-numbered questions, the process involves subtracting one from each score, whereas for even-numbered questions, the score is subtracted from five, resulting in adjusted values that fall between 0 and 4. These adjusted values are subsequently summed together, and the total is multiplied by 2.5 to derive the final SUS score, with higher scores reflecting superior usability.(x)**Cueing preference:** Lastly, participants are asked a question to determine preferred cueing modality, “Which cueing do you prefer, was it metronome, instrumental music or vocal music?”

